#### Develop and distribute educational materials

Targeted at principals to address perceived barriers to adoption, the strategy will initially aim to create tension for change (e.g., via outlining parent and carer interest and expectations); and then communicate the attractive program attributes (e.g., simplicity, no-cost). This communication will consist of up to two contacts, including a printed information pack (consisting of a flyer, SWAP IT pen and example parent booklet) at the commencement of the intervention period followed by an email to promote the program. As an additional strategy, one LHD will offer printed parent booklets promoting the SWAP IT program to all parents and carers with children commencing the following school year within their school kindergarten orientation packs along with a flyer encouraging the school principal or wellbeing coordinator to adopt the program.

#### Local opinion leaders

Promotional materials, including one printed information pack (consisting of a flyer and example SWAP IT parent booklet) and one email, will be delivered to other leaders that may be influential in a schools decision to adopt health promotion programs, specifically the school administration manager and parent committee. The aim of these materials is to promote the SWAP IT program and encourage school adoption.

#### Audit and feedback

Data and feedback on school adoption of SWAP IT will be automatically captured through electronic registration records and be provided to schools via other implementation strategies, including educational materials, local facilitation and local opinion leaders. For example, educational materials provided to principals, school administration managers and parent committees will include information on the number of schools that have registered for SWAP IT, a link to view an online list of schools have already adopted the program (to create tension for change and social norms) and provide instruction on how the school can also register for the program.

#### Educational meeting

Health promotion staff from LHDs will conduct one webinar with schools within their LHD to assess interest in the SWAP IT program and address any barriers to adoption. Webinar content will be developed by the research team in collaboration with health promotion staff.

### Control group and contamination

Registration for the SWAP IT program is publicly available and freely accessible for all schools, including schools allocated to the control group. The implementation strategies to be delivered to the control group across LHDs is described in Table 1. For most schools allocated to the control group, the comparison will be ‘no implementation support’ or a singular strategy. Execution of the implementation strategies will be monitored centrally by the research team in consultation with health promotion staff from each LHD to minimize risk of contamination. Nonetheless, school exposure to the implementation strategies will be assessed at follow-up via an online or telephone survey with school principals (described below).

### Study outcomes and data collection

Trial outcomes were discussed and agreed upon by participating LHDs (Table 3). Data collection for all trial outcomes were harmonized across all LHDs and will be collected centrally by the research team at the University of Newcastle. The centralisation of data collection represented an efficient means of collecting and managing data for all participating LHDs. All demographic, operational and trial outcome measures are harmonized (i.e., identical item, measure and data collection method) to facilitate comparability and analysis. Each participating LHD will retain access to their trial dataset.

**Table 3 tab3:** Study outcomes and sample assessed.

Outcome	Timepoint	Study sample assessed
Adoption of the SWAP IT program	Baseline and 9 months post baseline	All schools within the study sample
Acceptability of the implementation strategies	9 months post baseline	Sub-sample of 243 schools
Implementation of the SWAP IT program	9 months post baseline	Schools within the sub-sample of 243 that have adopted SWAP IT
Sustainability of the SWAP IT program	18 months post baseline	All schools within the study sample that have adopted SWAP IT
School characteristics	Baseline	All schools within the study sample

#### Primary outcome

Adoption of the SWAP IT program, defined as the number of schools who register for the lunchbox nutrition program (SWAP IT), will be assessed within schools allocated to the intervention and control group via electronic registration records captured automatically following school registration to SWAP IT. No additional data collection is required to assess the primary outcome. As part of the registration process, schools provide consent for the de-identified registration data to be used for research and evaluation purposes. This outcome will be assessed at baseline and approximately 9 months after baseline data collection.

#### Secondary outcomes

Acceptability of implementation strategies, defined as the perception among principals that the implementation strategies are agreeable, palatable or satisfactory, will be assessed in a telephone or online survey with school principals at 9-month follow-up. School principals will be asked if they recall receiving each of the implementation strategies during the intervention period. For strategies the participants recall receiving, they will be asked to rate how acceptable they found the strategy on a 5-point Likert scale (1 = not acceptable; 5 = very acceptable) (38). Principals from 243 Catholic and Independent primary schools located across five LHDs (LHD 1; LHD 5; LHD 7; LHD 8; LHD 9) will be invited to participate in the survey. These LHDs have been selected as they are employing diverse combinations of the implementation strategies (Table 1). Including schools from these LHDs in the survey will ensure the acceptability of all employed strategies (across the 10 LHDs) will be assessed and ensures the data collection remains feasible to be conducted within the study timeline.

Implementation of the SWAP IT program, defined as the extent to which the SWAP IT program components were delivered by the school to parents, will be assessed in the telephone or online survey (described above) with a sub-sample of 243 school principals at 9-months follow-up. Schools will be asked to report if they implemented the SWAP IT program at their school, and what program components were implemented (i.e., parent messages; school lunchbox guidelines; curriculum resources; parent and carer resources).

Sustainability of the SWAP IT program, defined as continued school use of the lunchbox nutrition program (SWAP IT) at 18 months after baseline data collection, will be assessed via electronic registration records captured automatically following school registration to SWAP IT.

School characteristics, including postcode, total student enrolments, geographic location (urban, regional, rural and remote), proportion of Aboriginal student enrolments, and proportion of students that speak a language other than English at home, were obtained from a publically accessible Australian Curriculum, Assessment and Reporting Authority (ACARA) database (39).

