All schools that meet the eligibility criteria outlined above will be included in the study as part of usual service delivery provided by LHD health promotion staff to support schools to implement a range of healthy eating and physical activity policies and practices. Eligible schools will be invited to participate in the secondary data collection component of the study, specifically the follow-up survey conducted with school principals (described below). Schools will be recruited for the follow-up data collection via an invitation email containing a link to an online survey and a study information statement outlining the purpose of the research and their involvement. Schools that are yet to complete the survey will receive up to three reminder prompts via telephone or email by the research team to encourage completion. Recruitment for the data collection component commenced in November 2023 and concluded in December 2023.

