### Implementation strategies

A series of implementation strategies were developed with the aim of maximizing school adoption of the SWAP IT program in eligible schools that have not yet adopted the program. These implementation strategies were developed for each of the LHDs independently, based on their existing capacities and local contexts. Implementation strategies for each participating LHD (‘site’) were co-designed by LHD health promotion staff and other stakeholders, with support provided by National Centre of Implementation Science (NCOIS) implementation scientists and SWAP IT developers from the University of Newcastle. The development process included: (i) planning workshops facilitated by University staff that drew on tacit knowledge and experience of health promotion staff who had considerable experience working with schools; (ii) evidence regarding barriers to school adoption and implementation of SWAP IT collected by the research team as part of previous SWAP IT trials, (iii) data from systematic reviews and pilot trials regarding the effectiveness of strategies to facilitate adoption (32). During the workshops, theoretical framework tools were used to facilitate the selection of strategies to address barriers that were aligned to individual LHD capacity and contexts (35–37). Processes may have also been undertaken by LHDs to identify strategies to support access and engagement of priority populations within their region to ensure school adoption and implementation of SWAP IT does not further exacerbate health inequities. This may have included consultation and engagement processes with Aboriginal, or Culturally and Linguistically Diverse individuals, groups or stakeholders.

Across the 10 participating LHDs, six broad implementation strategies to maximize school adoption of SWAP IT emerged. The combination of these six strategies employed by each LHD will differ and will be executed over a period of 6 months. Once a school adopts SWAP IT, they will not receive any subsequent implementation strategies, and will select which school term they would prefer to receive the program. The SWAP IT messages are delivered weekly to parents and carers via usual school-parent communication channels for one school term (one message per week), followed by two messages per term on an ongoing basis. A school must adopt SWAP IT in order to receive the program.

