The implementation strategies executed by each LHD are described below and in Table 1, with the timeline for the delivery of the implementation strategies outlined in Table 2.

**Table 1 tab1:** Implementation strategies delivered by each Local Health District.

Local Health District	Group	Sector support and endorsement	Local facilitation	Educational meetings	Educational materials	Local opinion leaders	Audit and feedback
LHD 1	Intervention						
	Control						

LHD 2	Intervention						
	Control						

LHD 3	Intervention						
	Control						

LHD 4	Intervention						
	Control						

LHD 5	Intervention						
	Control						

LHD 6	Intervention						
	Control						

LHD 7	Intervention						
	Control						

LHD 8	Intervention						
	Control						

LHD 9	Intervention						
	Control						

LHD 10	Intervention						
	Control						

**Table 2 tab2:** Timeline for the delivery of the implementation strategies.

School Term	TERM 2 2023											SCHOOL HOLIDAY		TERM 3 2023										SCHOOL HOLIDAY		TERM 4 2023			
Term week	1		2	3	4	5	6	7	8	9	10	1	2	1	2	3	4	5	6	7	8	9	10	1	2	1	2	3	4
Strategy	Local-level Health endorsement letter	Printed information pack				Webinar	Tailored contact one							Tailored contact two							Admin manager email	Parent committee pack	Email		State-level Health endorsement letter				

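### The implementation denominator is all adopters, including those whose chosen start term may not have begun at the single November–December 2023 survey

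*Protocol article*

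**What the plan says.** All of this comes from the protocol article.

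- **Definition** (Secondary outcomes). Implementation is "defined as the extent to which the SWAP IT program components were delivered by the school to parents". It is asked in the principal survey labelled as the 9-month follow-up: "Schools will be asked to report if they implemented the SWAP IT program at their school, and what program components were implemented".
- **Denominator** (Study outcomes and data collection, Table 3). The sample assessed for implementation is "Schools within the sub-sample of 243 that have adopted SWAP IT".
- **Survey date** (Sample and participants). "Recruitment for the data collection component commenced in November 2023 and concluded in December 2023".
- **Start of the program** (Implementation strategies). A school that adopts "will select which school term they would prefer to receive the program". Messages then go out weekly "for one school term (one message per week), followed by two messages per term on an ongoing basis".
- **Strategy calendar** (Implementation strategies, Table 2). The strategies "will be executed over a period of 6 months", and the calendar in Table 2 opens in Term 2 2023, with a header that extends to Term 4 week 4.
- **Analysis** (Sample size and data analysis). Descriptive statistics are the only method named for implementation.

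**The concern.** Registering for SWAP IT and delivering it are separate events, and the school sets the gap between them. The survey looks once, at a fixed calendar time, at whether delivery has happened. The denominator depends on registration alone.

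A school that registered late and picked a term not yet begun is an adopter with nothing to report. It has not failed to deliver, because its delivery is not yet due. Placed in the same denominator as schools whose term came and went without delivery, it makes the proportion hard to read. A low figure could mean that schools register and then do not follow through, or only that many of them registered late and scheduled ahead. For a program being taken to scale these call for different responses.

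**Working it through.** The plan states no expected value or precision for implementation; its sample size statement concerns adoption only. The check therefore sets the dates beside the denominator and then illustrates the effect.

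**1. When schools are prompted to adopt.** As extracted, Table 2 lists nine contacts. The information pack, the webinar and both tailored contacts fall no later than about Term 3 week 1. The last four (administration manager email, parent committee pack, a further email, state-level endorsement letter) fall from about Term 3 week 8 to the holiday before Term 4. Column alignment in the extracted table is uncertain, so these positions are approximate.

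**2. When a school can start.** A school responding to the early contacts could have started in Term 3 or Term 4 2023. A school responding to the last four could hardly start before Term 4 2023, and nothing stops it choosing a 2024 term.

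**3. When implementation is asked.** Once, in November–December 2023, which I take to lie in Term 4 or just after it. A school with a 2024 start then has nothing delivered. A school that started in Term 4 may still be in its first, weekly phase.

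**4. Who is in the denominator.** Every adopter in the sub-sample, whether or not its term has begun.

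Steps 1 to 4 together put not-yet-due schools in the denominator with no possible delivery.

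**5. Direction and illustration.** Let *p* be the proportion implementing among due adopters and *f* the share of adopters not yet due. If the latter report nothing delivered, then

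reported proportion = *p* × (1 − *f*) + 0 × *f* = *p* × (1 − *f*).

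This is below *p* whenever *f* > 0 and *p* > 0. The documents give neither *p* nor *f*; the values below are assumed.

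| *f* | *p* = 90% | *p* = 70% |
|---|---|---|
| 0% | 90% | 70% |
| 10% | 0.90 × 0.90 = 81% | 0.70 × 0.90 = 63% |
| 20% | 0.90 × 0.80 = 72% | 0.70 × 0.80 = 56% |
| 30% | 0.90 × 0.70 = 63% | 0.70 × 0.70 = 49% |

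**6. Rough size of the denominator.** The sample size scenario is 10% adoption in the comparison group and a 30-point difference, so 40% in the intervention group. At 1:1 allocation the average over both groups is (10% + 40%) / 2 = 25%, and 243 × 0.25 ≈ 61 adopters before survey non-response. If adoption were 10% throughout, 243 × 0.10 ≈ 24. With 61 adopters, about 6 not-yet-due schools correspond to *f* = 10% and about 12 to *f* = 20%.

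**The case against.** The strongest reply has four parts.

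*No text says how such schools are scored.* A reader might infer that not-yet-due schools are recorded as non-implementers. The article does not say so. It summarises a survey item and gives no scoring rule, and the questionnaire and any analysis plan are not shown; either could hold a response option for scheduled schools. This stands, and the point is not put that way. What remains is the denominator that Table 3 does state, which takes no account of the start term.

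*Schools pick a preferred term, not a later one.* This also stands. Early adopters could have completed a full term by the survey, and even late responders might choose Term 4. The number affected may be small.

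*A snapshot at 9 months is a coherent outcome.* Delivery by a given time among all adopters is a legitimate quantity, with scheduling delay as part of it. This stands in part. It is a reason to keep the all-adopter figure, but that figure alone cannot separate delay from failure to deliver.

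*The outcome is minor.* Implementation is secondary, is not among the numbered objectives and is described only. This limits the weight of the point without removing it.

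Three stronger readings are tempting and not supported:

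- That the distortion differs between arms or Local Health Districts. This would require knowing who receives the late strategies, and the cells of Table 1 are blank in the text at hand.
- That the denominator could reach about 97 schools (243 × 0.40). That applies the intervention-group rate to a sub-sample that is not described as confined to that group.
- That a November–December survey contradicts the 9-month label. The baseline date is not given, so no conflict can be shown.

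**Conclusion.** The point holds in a limited form. As written, the implementation proportion has all sub-sample adopters as its denominator, is measured once in a survey recruited in November–December 2023, and can include schools whose chosen term had not begun. It then mixes not yet due with not delivered, and any such mixing lowers it.

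The size cannot be estimated from the documents. The drop from 90% to 81% or 72% rests on assumed shares of 10% and 20% not yet due, and on those schools reporting nothing delivered. The timing argument rests on an uncertain reading of the columns in Table 2, but the free choice of term and the stated denominator do not depend on it.

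The consequence is confined to one descriptive secondary outcome. The primary adoption analysis and the network meta-analysis of adoption are untouched.

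**What to change.** Use the start term each adopter selected to classify it as due (term begun) or not yet due on the date it answered the survey. Then:

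- report implementation, overall and by program component, among due schools;
- show the number of not-yet-due schools separately, marked as not assessed;
- keep the all-adopter proportion alongside, labelled as a snapshot at the 9-month survey;
- amend the implementation row of Table 3 to match.

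This can be done after the survey has closed, because it rests on a choice the school made on adopting. The article does not say that the selected term is held in the trial dataset, so that must be confirmed and the field linked if it is stored elsewhere. The cost is a somewhat smaller denominator for the main implementation figure, and so a wider interval around it. Randomization, sample size and the primary analysis do not change.

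Assessing the not-yet-due schools at 18 months is not part of this proposal. The sustainability outcome at that time comes from registration records, which are not described as recording the components delivered, so it would need a new survey.

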### Sample size and data analysis

We are anticipating a sample of at least 30 schools per group (and an average of 60 per group) in trials of each of the 10 participating LHDs. Descriptive statistics, including proportions, means and standard deviations, will be used to describe school characteristics, adoption, implementation and sustainability of SWAP IT, as well as the acceptability of the implementation strategies.

Analyses of trial outcomes will be undertaken under an intention to treat framework separately for each trial. For assessment of school level program adoption, the primary trial outcome, between-group differences, will be assessed using logistic regression. The model will include a term for treatment group (intervention vs. control) and pre-specified covariates prognostic of the outcome. Little, if any, missing primary outcome data is anticipated at follow-up, as program adoption is recorded automatically for all participating schools. Nonetheless, we will employ multiple imputation for any missing data in the event that schools withdraw from the study and request that their data are not used. All statistical tests will be 2 tailed with alpha of 0.05. Assuming adoption of the program by 10% in the comparison group, a sample size of approximately 30 schools per group will be sufficient to detect an absolute difference between groups of 30%, with 80% power and an alpha of 0.05.

We will employ component IPD component network meta-analysis to compare and rank the effects from all the tested strategies on the primary trial outcome (40). For this analysis we will also include the three randomized controlled trials from the pilot, (26) expanding the network and providing pooled individual level data from 13 randomized controlled trials. We will explore combining ‘educational meetings and educational materials’ into a single component for analysis given their shared underlying behavioral targets. We will adjust for prognostic factors and exploration of strategy—covariate interactions to identify if and to what extent effects vary by participant, population or other contextual factors (effect modifier) (40). We will also employ component network meta-analyses to model additive main effects (separate effects for each element or component of an implementation strategy); two way interactions (synergistic/antagonistic effects of components), and full interactions (different effects from each combination of components). The analyses will be performed under a Bayesian framework. There are no established methods for sample size calculations for component network meta-analysis.

For the secondary outcomes assessed via an online or telephone survey, data screening strategies were employed during survey development to minimize incomplete or inaccurate responses. These strategies included the use of mandatory fields (i.e., participants were unable to leave a survey item blank, but could select ‘prefer not to say’), minimizing the inclusion of open responses and reducing the survey length. Best practice recommendations for data screening will also be employed following data collection, including visually inspecting data to identify data entry errors or implausible values for each variable, and calculating distributional characteristics of items to assist in identifying outliers or extreme values (41).

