### Randomization and blinding

Prior to the delivery of the first scale-up strategy, schools within each LHD will be randomly allocated to either the intervention or control condition using a computerized random number function in a 1:1 (intervention: control) ratio. Randomization will be stratified by school size and social socio-economic location, as determined by Socio-Economic Indexes for Areas categorization using school postcodes, (33) given the socio-economic association with implementation of school nutrition programs (34). Randomization will be completed by a statistician not otherwise involved in the trial. Due to the nature of the intervention, participants will not be blinded to group allocation. However, research staff assessing the outcomes at follow-up will be blinded.

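### In the smallest LHD trials the primary logistic model expects about 3 control adopters, and the plan names neither a sparse-data method nor the two randomisation strata as covariates

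*Protocol article*

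**What the plan says.** In the Protocol article, under Sample size and data analysis, the outcomes of each LHD trial are analysed separately by intention to treat. For school adoption, the primary outcome, "between-group differences, will be assessed using logistic regression". On content, "The model will include a term for treatment group (intervention vs. control) and pre-specified covariates prognostic of the outcome". On error rate, "All statistical tests will be 2 tailed with alpha of 0.05". No estimator, test statistic or covariate name is given.

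On size, the same section says "We are anticipating a sample of at least 30 schools per group", with an average of 60 per group. It justifies 30 as follows: "Assuming adoption of the program by 10% in the comparison group", about 30 per group is "sufficient to detect an absolute difference between groups of 30%, with 80% power and an alpha of 0.05".

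Under Randomization and blinding, allocation is 1:1 within each LHD, and "Randomization will be stratified by school size and social socio-economic location". The reason given is prognostic: "given the socio-economic association with implementation of school nutrition programs". The analysis section does not mention these two variables again.

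**The concern.** Two matters are left open in the primary analysis of every LHD trial. They have different consequences.

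The first is sparse data. Each LHD is analysed on its own, so a small one borrows nothing from the others. The Bayesian pooled analysis serves a secondary objective. With about 3 expected events in the control arm, maximum-likelihood logistic regression is outside the range where its large-sample tests can be trusted. The Wald test becomes very conservative and the likelihood-ratio test somewhat liberal. An arm with no adopters gives an infinite odds ratio. In a small LHD, the conclusion could then depend on which p-value the software prints.

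The second is the link between design and analysis. Variables used to stratify randomisation because they are thought prognostic would normally be in the model. Naming them makes the analysis match the randomisation, and it recovers power if they really are prognostic.

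**Working it through.** **Inputs from the article.** Comparison adoption 10%; difference to detect 30 points, so 10% vs 40%; two-sided alpha 0.05; power 80%; minimum 30 and average 60 schools per group; 1:1 allocation. The 1,342 eligible schools over 10 trials of two groups give 1,342/20 = 67 per group, consistent with the stated average.

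**The plan's own figure.** The usual two-proportion formula with pooled null variance gives

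n = [1.960·√(2·0.25·0.75) + 0.842·√(0.1·0.9 + 0.4·0.6)]² / 0.30² = (1.200 + 0.483)² / 0.09 = 31.5, i.e. 32 per group.

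The unpooled form gives 7.849·0.33/0.09 = 28.8 and the arcsine form 29.8. Power at 30 per group by the pooled formula is 78.0%. The stated figure of approximately 30 therefore reproduces.

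**Expected events and empty arms.**
- Expected control adopters: 30·0.10 = 3; 60·0.10 = 6.
- Probability of no control adopter: 0.9³⁰ = 4.2%; 0.9⁶⁰ = 0.18%.
- Probability that at least one arm has no adopter when both rates are 10%: 1 − (1 − 0.9³⁰)² = 8.3% at 30 per group.

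An empty arm means that the maximum-likelihood odds ratio for treatment is not finite.

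**Exact size and power without covariates.** Every possible pair of adopter counts was enumerated with its binomial probability. The tests were:
- Wald: |log OR| / √(1/a + 1/b + 1/c + 1/d) > 1.96. A table with an empty cell counts as no rejection, because the standard error diverges.
- Likelihood ratio: twice the log-likelihood difference > 3.84.
- Firth: twice the penalised log-likelihood difference > 3.84, with the same ½·log-determinant penalty in both fits.

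| Schools per group | Test | Type I error, 10% in both arms | Power, 10% vs 40% |
|---|---|---|---|
| 30 | Wald | 0.85% | 72.6% |
| 30 | Likelihood ratio | 7.5% | 82.2% |
| 30 | Firth penalised likelihood ratio | 4.1% | 79.4% |
| 60 | Wald | 2.9% | 97.6% |
| 60 | Likelihood ratio | 6.1% | 98.0% |

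**Effect of adjusting for the strata.** The article gives no stratum effects. Two binary stratifiers were therefore assumed, each with odds ratio 1, 2 or 4, and trials of 30 per group with stratified allocation were simulated (5,000 null runs and 4,000 runs at 10% vs 40% per setting).

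| Analysis | Type I error | Power for stratum odds ratios 1 / 2 / 4 |
|---|---|---|
| Unadjusted, Wald | 0.5–0.8% | 73% / 71% / 72% |
| Strata-adjusted, Wald | 0.8–1.0% | 74% / 76% / 81% |
| Strata-adjusted, likelihood ratio | 7.5–8.2% | 82% / 83% / 87% |
| Strata-adjusted, Firth | 4.0–4.3% | 79% / 80% / 85% |

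Adding the strata raises power where they are prognostic but does not correct the type I error under maximum likelihood. The penalised fit does that.

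**The case against.** The strongest objection is that the article is a condensed document. It says that the covariates are pre-specified. A covariate list, a choice of test and the handling of sparse data are commonly left to a full protocol or analysis plan that is not shown. This stands as far as silence alone goes: an unprinted list is not an error. What remains is that the article itself fixes the model class, separate analysis of each LHD, alpha 0.05 and the sufficiency of 30 schools per group. Those commitments already put the smallest trials where the usual fit does not deliver the stated error rate.

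Three stronger readings are tempting, and the document does not support them.
- A reader might infer that the plan specifies ordinary maximum likelihood. It says only logistic regression; the estimator is the usual meaning of that term, not a stated choice.
- A reader might infer that the strata are ignored. They are unnamed, not excluded. The prognostic reason given for stratifying suggests that socio-economic location at least is intended as a covariate, and nothing says that school size is left out.
- A reader might infer that all ten trials are affected alike. Thirty per group is the minimum; at the average of 60 little is lost.

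It is also fair to say that Firth's method is one of several acceptable sparse-data options.

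**Conclusion.** The point holds in a limited form. In an LHD near 30 schools per group with 10% comparison adoption, a conventional maximum-likelihood fit would test at 0.85% (Wald) or 7.5% (likelihood ratio) instead of 5%. It would give no finite odds ratio in about 4% of trials at the planned effect and 8% under the null. Power falls short of 80% only with the Wald test (about 73%); the likelihood-ratio test has 82%, but at an inflated error rate. At 60 per group the departures are small.

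A reader might take this to mean that the sample size is wrong. It is not: it reproduces.

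The size and power figures without covariates rest only on the article's own inputs and on reading logistic regression as maximum likelihood. The gain from adjustment, from almost nothing to about 9 points of Wald power, depends on assumed stratum effects. The article does not say how many LHDs lie near the minimum. This is an improvement worth making before analysis, not a flaw that undermines the trial.

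**What to change.** State in the analysis section that:
- each LHD model contains treatment group and the two stratification variables, school size and socio-economic category, and that any further covariates are few and named;
- each model is fitted by Firth penalised likelihood, with profile-likelihood p-values and confidence intervals, in all LHDs so that the method does not depend on the counts observed.

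Profile-likelihood inference is part of the proposal: at 30 per group a Wald test on the Firth estimate is still far too conservative (type I error 1.1%, power 76.7%, no covariates). Reporting a risk difference beside the odds ratio would match the planning effect but is optional.

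The cost is one paragraph, with no new data and no change to the sample size. The one drawback is an estimator that some readers know less well.
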